#### Secondary outcome measures

##### Physical function assessment

The Osteoarthritis is assessed using the Western Ontario and McMaster Universities Osteoarthritis Index (WOMAC), a total of 24 questions, by patient self-evaluation, Scores range from 0 (no symptoms) to 4 (very severe) on a scale from 0 to 96, with higher scores indicating more severe pain and dysfunction [27].

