## Methods

### Primary objective {7}

The primary objective of this study is to assess the effect of telemedicine-supported multicomponent exercise therapy on pain management in patients with knee osteoarthritis in comparison to usual care therapy.

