### Secondary objectives {7}

i)Evaluate the effects of telemedicine-supported multicomponent exercise therapy on physical function and quality of life in knee osteoarthritis patients compared to usual care.ii)Assess the impact of multicomponent exercise therapy on self-cognition, mental health status, and the reduction of pain fear and pain catastrophic imagery in patients with knee osteoarthritis.iii)Determine the level of adherence to multicomponent exercise therapy among KOA patients who self-manage their condition at home. 

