### Outcome measures {12}

After obtaining informed consent, a baseline assessment will be conducted. The details gathered include participants’age (acquired using the birthdate shown on their ID cards), gender, height, weight, BMI, education level, occupation, income source, hobbies, interests, marital status, smoking and alcohol use, medical history, knee pain duration, pain severity (current, worst, mildest), triggers, alleviating factors, and pain-avoiding behaviors. The primary and secondary outcomes will be evaluated before commencing the trial (baseline) and at 4-, 8- and 12-week post-intervention (shown in Table 2). We focus on changes in outcomes at 12 weeks after treatment.

**Table 2 Tab2:** Overview of the measurements and timing of measurements

Domain	Reporting methods	Questionnaire line	Base	4 weeks	8 weeks	12 weeks
Demographic characteristics	Self-reported	Purpose built	√	-	-	-
Pain intensity	Self-reported	VAS	√	√	√	√
Physical function	Self-reported	WOMAC	√	√	√	√
	Walking ability	TUG	√	√	√	√
Quality of life	Self-reported	SF-36	√	√	√	√
Self-efficacy	Self-reported	PSEQ	√	√	√	√
Mental health status	Self-reported	DASS21	√	√	√	√
Fear-avoidance in exercise	Self-reported	TSK	√	√	√	√
Pain catastrophic imagery	Self-reported	PCS	√	√	√	√
Exercise adherence	Self-reported	EARS	-	√	√	√
	Events	Movement completion rate	-	√	√	√
Adeverse events	Self-reported	-	-	√	√	√

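### The self-reported measure of physical function is the all-item WOMAC total, which also scores pain, so pain relief alone could contribute to an apparent gain in function

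*Protocol article*

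**What the plan says.** The protocol article keeps pain and function apart in its objectives. The primary objective is the effect "on pain management in patients with knee osteoarthritis in comparison to usual care therapy". Secondary objective (i) covers "effects of telemedicine-supported multicomponent exercise therapy on physical function and quality of life".

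The section headed Physical function assessment assigns the WOMAC and describes it as "a total of 24 questions, by patient self-evaluation". Each item is scored from 0 to 4, and the result is placed "on a scale from 0 to 96", "with higher scores indicating more severe pain and dysfunction".

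Table 2, under Outcome measures {12}, repeats the assignment in the row "Physical function Self-reported WOMAC". The only other entry in that domain is "Walking ability TUG", the timed walking test. Neither place names a WOMAC function subscore or says that the pain items are scored apart.

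The statistical methods section {20a} does not mention the WOMAC by name. It does say that an effect size will be calculated for all outcome indicators and judged by Cohen's criteria.

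**The concern.** The score chosen for function is, in the protocol's own description, a mix of function and pain. Pain is already the construct of the primary outcome, so the self-reported function measure partly repeats the primary outcome.

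What is at stake is the reading of secondary objective (i). The intervention is aimed at pain. If pain falls and function does not change, the WOMAC total still falls. Its effect size would then be graded under the physical function domain, and nothing in the stated score shows how much of the shift came from pain items.

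**Working it through.** **Inputs from the protocol article**
- Number of WOMAC items: 24; score per item: 0 to 4; stated range: 0 to 96 (Physical function assessment).
- Meaning of the score: pain and dysfunction together (same section).
- Domain label: physical function (Table 2).
- Minimum clinically important difference for the VAS: 18 mm on 100 mm (section {20a}).
- Boundary for a small effect: 0.2 (Sample size calculation {14}).

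**Step 1: reproduce the stated range.** Items × maximum item score = 24 × 4 = 96. This matches exactly. Only the sum of all 24 items can reach 96, so the score described is the full total and not a function subscore.

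**Step 2: follow a pain-only change.** Let k be the number of pain items and δ the mean fall on each, with every other item fixed. The total falls by k × δ although function has not changed. The document does not give k, so it is varied here as an assumption. With δ = 1:

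| Pain items assumed (k) | Fall in total | Share of 96 |
|---|---|---|
| 3 | 3 | 3.1% |
| 5 | 5 | 5.2% |
| 8 | 8 | 8.3% |

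**Step 3: gauge the dilution.** Suppose each pain item falls by the same share of its scale as the protocol's VAS threshold: δ = 0.18 × 4 = 0.72. The total then falls by 3 × 0.72 = 2.16, 5 × 0.72 = 3.60 or 8 × 0.72 = 5.76 points, which is 2.25%, 3.75% or 6.0% of 96. An 18% fall in pain thus appears as a 2.25% to 6.0% fall in the total.

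**Step 4: an illustrative standardised size.** No standard deviation is given for the WOMAC. Assume an SD of 1 per item and an inter-item correlation r of 0.4 or 0.6. The SD of the total is √(24 + 24 × 23 × r), which is √244.8 = 15.65 or √355.2 = 18.85. The standardised shift, with power for a simple two-group comparison of means at two-sided 5% and 32 per arm (the calculated 64, split 1:1), is:

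| k | r = 0.4: shift (power) | r = 0.6: shift (power) |
|---|---|---|
| 3 | 2.16 / 15.65 = 0.14 (8%) | 2.16 / 18.85 = 0.11 (7%) |
| 5 | 3.60 / 15.65 = 0.23 (15%) | 3.60 / 18.85 = 0.19 (12%) |
| 8 | 5.76 / 15.65 = 0.37 (31%) | 5.76 / 18.85 = 0.31 (23%) |

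Under these assumptions a pain-only change lies on either side of the protocol's 0.2 boundary and would usually not be significant by itself. It would add to, or be mistaken for, a function effect of modest size. The table shows the mechanism at work; it is not an estimate for this trial.

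**The case against.** The strongest reply is that the section describes an instrument and does not fix an analysis. The statistical methods never name a WOMAC score, and which score of a multi-part questionnaire is tested is commonly left to the full protocol or the SAP, neither of which is shown. This has some weight. However, the article does more than leave the matter open. It gives one score, one range and one interpretation, under a heading and a table row that both label it physical function. Elsewhere it does describe components: it names the three PCS subscales and says which EARS subscales are scored. A stated score that does not match its objective is a fair subject for comment.

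The second reply is that function is not left to the WOMAC alone. TUG is measured at every assessment in the same domain, and the SF-36 has a body function dimension. This stands as a partial check. It does not show whether pain items or function items moved the WOMAC total if the measures disagree.

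The third reply is that the effect is diluted and its size unknown. This stands in full. Three stronger readings are tempting and are not supported:
- A reader might infer that a pure pain effect would be reported as a function gain. The shift need not reach significance, so could contribute is the most that can be said.
- A reader might infer that secondary objective (i) cannot be answered. The total still reflects dysfunction, and TUG and the SF-36 dimension also inform the objective.
- A reader might attach a large standardised effect to the problem, for example 7 × 1 / 12 = 0.58. That figure combines seven assumed non-function items, a full-point fall on each and an assumed SD of 12. The document gives none of these and does not show that all such items concern pain.

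**Conclusion.** The point holds in a limited form. The protocol article assigns the all-item WOMAC total, which it says reflects both pain and dysfunction, as the self-reported measure of physical function. A reduction in pain alone would move that score and could contribute to an apparent function benefit.

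That the score is the full total rests on 24 × 4 = 96 and needs no assumption. That pain relief moves it rests on the protocol's own description, with the natural reading that some of the 24 items ask about pain. The size of the effect cannot be derived from the document, because every figure beyond the range of 96 depends on an assumed item split, item shift or SD.

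The matter touches one of two measures in one secondary domain. The primary outcome, the sample size and the data collection are unaffected. It is worth changing because the gain in interpretability is free.

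**What to change.** In the section Physical function assessment and in Table 2, name the WOMAC physical function items, scored as a function subscore, as the self-report outcome for secondary objective (i), alongside TUG. State which items form that subscore and its range. Report the pain items and the 0 to 96 total separately, with the total labelled as overall symptom severity.

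The cost is a scoring line and a changed outcome label. All 24 items are already collected at baseline and at 4, 8 and 12 weeks, so no visit, questionnaire or participant is added. The change should be recorded before the outcome data are analysed.

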##### Walking ability test

The time up go test (TUG) is a quick assessment of functional walking ability [28]. At the time of assessment, the patient will be seated in a backrest chair with armrests (seat height approximately 45 cm, armrest height approximately 20 cm), with the body resting on the back of the chair and hands resting on the armrests. If using a walker such as a cane, place your hand on the walker. Paste colored strips or draw a clearly visible thick line or place an obvious mark on the ground 3 m away from the seat. After the tester gives the “go” command, the patient stands up from the back of the chair, stands on his or her footing, walks forward 3 m with the usual walking gait, passes the thick line or mark, turns around, walks back to the chair, and then turns and sits down, leaning against the back of the chair. During testing, no help can be provided. The tester records the time in seconds for the patient to stand up from the starting position (reclining) and sit down again and lean back. The patient may be asked to practice several times to understand the content of the test before the formal test. In addition, the patient’s risk of falling during the test period will be determined. The time criteria are < 10 s, free movement; < 20 s, most can move independently; 20–29 s, unstable movement; and > 30 s, dyskinesia. The risk criteria are as follows: 1 for normal, 2 for very slight abnormalities, 3 for mild abnormalities, 4 for moderate abnormalities, and 5 for severe abnormalities [29].

##### Quality of life

The MOS item short-form health survey (SF-36) is used to assess the quality of life, which includes 8 dimensions: body function, physiological function, body pain, general health status, the vitality of life, social function, emotional function, and mental health, a total of 36 questions, according to the standardized weight of the corresponding score, the score of each question is added to get the test rough score, through the score operation conversion formula specified in the scale to get the final score, the total range of 0–100 points. The higher the final score, the higher the quality of life [30].

##### Patients' self-efficacy for pain

The Pain Self-Efficacy Questionnaire(PSEQ) is used to assess the confidence of patients with persistent pain to perform activities in pain [31]. There are 10 items in the questionnaire, and the evaluation standard for each item ranges from 0 to 7 points. 0 points represent no confidence at all, 7 points represent complete confidence, and higher scores indicate that patients have higher self-efficacy beliefs about returning to life. The reliability and validity of the questionnaire have been verified [32].

##### Mental health status

Mental health status is measured by Depression-Anxiety-Stress Scale (DASS21). DASS21 is a mental health assessment scale based on the three-factor model of depression, anxiety, and stress. The scale takes the degree of various negative emotional states induced by the subject as the evaluation index and uses a 4-point scoring method. Non-conforming to the standard is “0”; “1” means sometimes satisfied, “2” means often satisfied, “3” means always satisfied, and higher scores indicate higher depression, anxiety, and stress indices [33].

##### Fear-avoidance in exercise

Tampa Scale of Kinesiophobia (TSK) is a 17-item scale developed to assess fear of movement/re-injury. The scale includes parameters of injury/re-injury and fear-avoidance in work-related activities [34].

##### Pain catastrophic imagery

The Pain Catastrophizing Scale (PCS) is a widely adopted self-report tool for assessing exaggerated negative conceptualization of persistent, anticipated, or imaged pain. The PCS is a 13-item questionnaire consisting of three subscales (helplessness, magnification, and rumination), with each item on the scale being scored on a 5-point Likert scale, with a score of 0 representing “never” and 4 for “always,” with higher scores indicating higher levels of pain catastrophizing [35].

##### Exercise adherence

The Exercise Adherence Rating Scale (EARS) is a 16-item scale developed to evaluate the adherence of individuals to the exercises recommended for individuals with chronic pain diseases, and the reasons for their compliance or non-compliance. It consists of 3 subscales. Subscale A does not participate in scoring. Subscale B (evaluates self-reported adherence to exercises) consists of 6 questions and subscale C (evaluates the reasons for compliance or non-compliance with the recommended exercise) consists of 10 questions, and these subscales are scored [36]. In addition, we will calculate the completion rate of exercise prescriptions for patients with KOA by the number of completed movements captured by the wearable devices.

### Adverse events {22}

Any issue in the study knee or elsewhere in the body that the participant believes to be related to their participation in the trial is recognized to be an adverse event, as long as at least one of the following conditions is present: (i) that led to the participant seeking medical attention for 2 days or longer; and (ii) that exacerbated pain and/or disability [37]. Based on prior experiments, the incidence of serious adverse events such as death or sudden severe illnesses among patients undergoing exercise therapy is extremely low. In the case of adverse events necessitating emergency assistance (e.g., sudden cardiovascular issues, falls, and dizziness), the physiotherapists, doctors, and the rescue team at West China Hospital will provide prompt emergency aid. Should an emergency arise at home, our research team will have previously furnished the patient with contact information for, or access to, medical facilities in their community. These institutions will partake in providing the necessary care. Post-treatment, the clinical coordinator will document the timing and methods of intervention for the adverse events. In non-emergency scenarios, patients are to report adverse events to the clinical coordinator, who will in turn inform the physiotherapists and rehabilitation doctors within the research team. Following a consensus discussion, a viable resolution will be devised for the patient, and the clinical coordinator will relay this solution to the affected individual. The time span from report to feedback will not exceed 8 h. A consolidated report of adverse events will be featured in the final study report, detailing the type and frequency of such events.

### Sample size calculation {14}

The sample size was calculated by G*power 3.1.9 according to the following conditions. According to Cohen’s criterion for effect size [38], 0.2, 0.5, and 0.8 are the boundary values for small, medium, and large effect sizes, respectively. According to Mecklenburg test results [39], 0.3 was selected to verify the small effect size, α was 0.05, the test power was 0.8, and the intraclass correlation coefficient was 0.6. The experiment will be performed with a two-way repeated measures analysis of variance, and the two groups will be measured four times. The final calculated sample size was 64. Considering a dropout rate of 25%, the actual required sample size should be 86.

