We will use IBM SPSS, version 26.0.1 for all statistical analyses, with 2-tailed tests as appropriate, and 2-sided *P* < 0.05 considered to be statistically significant. Baseline data on categorical variables (e.g., sex, occupation, education level) will be used to compare statistical differences between the trial and control groups using chi-square tests. For continuous variables (e.g., age, BMI, pain intensity, duration of knee pain), a normality test will be first conducted. If all groups meet normality, mean ± standard deviation (SD) will be used for statistical description, and two independent sample *T* tests or Mann–Whitney *U* tests will be used for comparison between groups. Otherwise, the median (interquartile spacing) will be used for statistical description, and a nonparametric test will be used for comparison between groups. If the results of the trial meet the conditions of homogeneity of variance and spherical symmetry, the two-factor four-level repeated measurement analysis of variance (group*time) is used; otherwise, the mixed effects model is used. According to the recommendations of the International Conference on Osteoarthropathy [42], the minimum clinically important difference (MCID) could be achieved when the pain intensity (primary outcome index: VAS) between the two groups is changed by 18 mm based on 100 mm. A chi-square test will be used to infer the proportion of the number of patients meeting the MCID between the two groups. The measurement results of all outcome indicators will calculate the effect size, and the size of the effect size between the two groups will be compared according to Cohen’s criteria [38] to draw the appropriate conclusions.

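### The sample size of 64 reproduces only with 0.3 as Cohen's f (d = 0.6), so the trial has about 29% power, not 80%, for the small effect (d = 0.3) the text describes

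*Protocol article*

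**What the plan says.** The protocol's section Sample size calculation {14} first sets a scale: "0.2, 0.5, and 0.8 are the boundary values for small, medium, and large effect sizes, respectively". It then places the design effect on that scale: "0.3 was selected to verify the small effect size, α was 0.05, the test power was 0.8". The other inputs are that "the intraclass correlation coefficient was 0.6" and that the analysis is a "two-way repeated measures analysis of variance, and the two groups will be measured four times", computed in G*Power 3.1.9. The result is given as "The final calculated sample size was 64", raised to 86 for 25% dropout. The section does not say whether 0.3 is d or f, or whether the group main effect or the group-by-time term was sized. Statistical methods for primary and secondary outcomes {20a} gives the testing level as "2-sided *P* < 0.05 considered to be statistically significant" and names the model as group by time.

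**The concern.** The cited boundaries are benchmarks for d, the difference between two means in standard deviation units. The G*Power ANOVA routines ask for f, which for two equal groups is half of d. A value of 0.3 is a fairly small effect as d but a more than medium effect as f. If the value was described on one scale and entered on the other, the trial is sized for an effect twice as large as the one it says it can detect.

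This matters for interpretation. The statistical methods section says that effect sizes for all outcomes will be judged by Cohen's criteria to reach conclusions. A reader who believes the trial had 80% power for a small effect may take a non-significant result as evidence against an effect of about 0.3, which the trial had little chance of detecting.

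**Working it through.** **Inputs.** From Sample size calculation {14}: effect size 0.3, level 0.05, power 0.80, correlation ρ = 0.6, k = 2 groups, m = 4 measurements, total N = 64, dropout 25%. From Design {8}: 1:1 allocation. From the statistical methods section: two-sided testing.

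**Formula.** For the between-groups test in a repeated-measures ANOVA, the noncentrality is λ = N·m·f² / (1 + (m − 1)ρ), with 1 and N − 2 degrees of freedom. Here 1 + 3 × 0.6 = 2.8. For two equal groups, f = d/2.

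**Step 1: reproduce the protocol's figure, with f = 0.3.**
- N = 62: λ = 62 × 4 × 0.09 / 2.8 = 7.97, power 0.793.
- N = 64: λ = 64 × 4 × 0.09 / 2.8 = 8.23, power 0.806.
- The smallest balanced total is therefore 64, as stated. Dropout: 64 / 0.75 = 85.3, rounded up to 86, also as stated.

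**Step 2: translate to d.** f = 0.3 gives d = 2 × 0.3 = 0.6, above the protocol's medium boundary of 0.5. On the usual benchmarks for f (0.1, 0.25, 0.4), 0.3 is also above medium. Neither scale makes this input small.

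**Step 3: take the text at its word, with d = 0.3 and so f = 0.15.**
- N = 64: λ = 64 × 4 × 0.0225 / 2.8 = 2.06, power 0.292.
- N = 86 with no dropout: λ = 2.76, power 0.376.
- 80% power: N = 246 gives 0.7998 and N = 248 gives 0.803, so 248 evaluable. Inflated for dropout, 248 / 0.75 = 330.7, or 331.
- At d = 0.2, the protocol's own boundary for small (f = 0.10), power at N = 64 is 0.156.

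**Step 4: could another routine have produced 64?** Totals needed for 80% power with the stated inputs:

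| Test and effect-size option | f = 0.30 | f = 0.15 |
|---|---|---|
| Between groups | **64** | 248 |
| Group by time, G*Power 3.0 option | 14 | 50 |
| Group by time, SPSS option | 44 | 166 |
| Group by time, Cohen option | 42 | 164 |
| Multivariate, G*Power 3.0 option | 18 | 54 |
| Multivariate, Cohen option | 126 | 490 |

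Only the between-groups test with f = 0.30 returns 64. The G*Power 3.0 group-by-time option at f = 0.15 comes near (N = 62) only with a nonsphericity correction of about 0.75, which the protocol does not state.

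**Step 5: does a different analysis of 64 participants reach 80% for d = 0.3?**
- Baseline-adjusted week-12 comparison: λ = (64/4) × 0.3² / (1 − 0.6²) = 2.25 on 1 and 61 df, power 0.31 (0.32 by normal approximation).
- Group by time, no difference at baseline and d = 0.3 at weeks 4, 8 and 12: the group effects are ±0.15 at three visits and 0 at baseline. Their squared deviations from the visit average of 0.1125 sum to 0.0169, so λ = 64 × 0.0169 / 0.4 = 2.70 on 3 and 186 df, power 0.24.

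Neither does.

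**The case against.** **The index is never named.** The authors may have meant f = 0.3 all along, in which case the 80% is real and only the benchmark sentence and the word small are wrong. This is fair, and the source trial's scale cannot be checked from the document. But the only scale the section offers for 0.3 is that of d, so the claim as printed is wrong on either reading.

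**The 29% belongs to one test.** It is the group effect averaged over four visits, whereas the protocol names group by time and focuses on 12 weeks. Power for the interaction depends on how the effect size is defined: at f = 0.15 and N = 64 it is about 0.37 to 0.38 under the SPSS and Cohen options and 0.90 under the G*Power 3.0 option. The 29% should therefore be tied to the test that yields 64. When d = 0.3 is specified directly as a difference between groups, power stays between 0.24 and 0.32 for the analyses above.

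**The equivalence of f = 0.3 and d = 0.6 needs a condition.** In the test that was sized, the difference must be 0.6 at all four visits, including baseline, where randomised groups should not differ. With 0 at baseline and 0.6 afterwards, the averaged f is 0.3 × 3/4 = 0.225 and power at 64 is 0.56. This stands, and the restatement should say so. For the analyses the protocol emphasises, d = 0.6 fares better: 0.79 for group by time and 0.84 for baseline-adjusted week 12.

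**The trial may be adequate for what matters clinically.** The protocol's important difference is 18 mm. No standard deviation is given. Assuming 20 to 30 mm, 18 mm is d = 0.6 to 0.9, with power of 0.84 to 0.99 for the adjusted week-12 test. This supports keeping the sample size. It does not support calling the target effect small.

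**Conclusion.** The concern holds. The figures 64 and 86 are computed correctly, but from f = 0.3, that is d = 0.6, while the text presents 0.3 as a small effect on the d scale. The claimed 80% power for a small effect is not a property of this design. For d = 0.3 and 64 evaluable participants, power is 29% in the test that yields 64, and 248 evaluable would be needed for 80%. These results assume ρ = 0.6 between all pairs of visits, equal groups and, for the 29%, a constant difference across the four visits. That 0.3 was entered as f is an inference, but it rests on an exact reproduction that no other standard option gives from the stated inputs. It must be corrected because it concerns the trial's headline power statement.

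**What to change.** Keep 86 randomised and 64 evaluable, and rewrite the justification in Sample size calculation {14}:

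- Name the index: effect size f = 0.3, equivalent to d = 0.6 (medium to large) for two equal groups when the difference is the same at every visit.
- State that the between-groups term was sized. It would help to add that with no baseline difference its power for d = 0.6 afterwards is about 56%, against about 79% for group by time and 84% for a baseline-adjusted week-12 comparison.
- Delete the word small, and remove the 0.2/0.5/0.8 boundaries as the justification for 0.3.
- State that power for d = 0.3 is about 30%, so a non-significant result does not exclude small effects.

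The cost is wording only. No participants are added, and conduct and analysis do not change. The stated sensitivity of the trial becomes less favourable.

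### The sample-size section does not name the powered effect; its 64 reproduces only as a group main effect averaged over four visits including baseline, so the 80% power does not carry over to group-by-time or week 12

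*Protocol article*

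**What the plan says.** All references are to the Protocol article.

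- **Sample size calculation {14}**: G*Power was used. The effect-size scale is introduced as "0.2, 0.5, and 0.8 are the boundary values for small, medium, and large effect sizes, respectively", and then "0.3 was selected to verify the small effect size, α was 0.05, the test power was 0.8", with an intraclass correlation of 0.6. The design is described as "The experiment will be performed with a two-way repeated measures analysis of variance, and the two groups will be measured four times". The result is 64, raised to 86 for 25% dropout. The section does not say whether the group, time or group-by-time effect was powered.
- **Abstract (Methods and analysis)** and **Table 2**: the four VAS measurements are baseline and weeks 4, 8 and 12.
- **Outcome measures {12}**: "We focus on changes in outcomes at 12 weeks after treatment".
- **Statistical methods for primary and secondary outcomes {20a}**: if homogeneity of variance and sphericity hold, "the two-factor four-level repeated measurement analysis of variance (group*time) is used"; otherwise a mixed effects model. The significance rule is "2-sided *P* < 0.05 considered to be statistically significant".

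**The concern.** A two-way repeated measures ANOVA gives three F tests (group, time, group-by-time), and their sample sizes differ widely for the same inputs. A power statement therefore means something only once the effect is named. A reader of this article will take the 80% as applying to the group-by-time analysis or to the 12-week change, since those are what the article points to.

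If the figure belongs to the group effect averaged over all four visits, one of the averaged measurements was taken before treatment, when randomisation makes the expected difference zero. That dilutes the effect being tested, and the trial then has no stated power for the comparison it emphasises.

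**Working it through.** **Inputs.** Effect 0.3, alpha 0.05, power 0.8, correlation ρ = 0.6, 2 groups, m = 4 measurements, N = 64, dropout 25% (Sample size calculation {14}); 1:1 allocation (Design {8}).

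**1. Reproducing 64 and 86.** G*Power's repeated-measures *between factors* test uses λ = f²·N·m / (1 + (m−1)ρ), with 1 and N−2 df.

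- N = 62: λ = 0.09 × 62 × 4 / 2.8 = 7.97, power 0.793.
- N = 64: λ = 0.09 × 64 × 4 / 2.8 = 8.23, power 0.806.

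The smallest even N reaching 80% is 64. Dropout: 64 / 0.75 = 85.3, rounded up to 86. Both stated figures are met exactly.

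**2. Other tests with the same inputs.** The default *within-between interaction* uses λ = f²·N·m / (1−ρ), with 3 and 3(N−2) df.

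- N = 12: λ = 10.8, power 0.736.
- N = 14: λ = 12.6, power 0.815.

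| Test | N for 80% power |
|---|---|
| Group main effect, 4 visits | 64 |
| Group main effect, 3 visits | 66 |
| Interaction, default option | 14 |
| Interaction, other effect-size conventions | 42 or 44 |
| Two-sample t test at week 12, d = 0.3 | 352 |
| Two-sample t test at week 12, d = 0.6 | 90 |

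With four measurements, only the group main effect returns 64.

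**3. What that effect size demands.** For two equal groups d = 2f, so f = 0.3 is a difference of 0.6 SD in the mean over four visits. With a baseline difference of 0 and a constant difference D afterwards, the mean is 3D/4. Setting 3D/4 = 0.6 gives D = 0.8 SD at each of weeks 4, 8 and 12.

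**4. Power at 64 evaluable for a true week-12 difference of 0.6 SD.** Assumptions made here, not by the protocol: SD 1, compound symmetry, ρ = 0.6, n = 32 per arm, and two illustrative profiles of the group difference over the four visits.

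- Main effect: λ = (n/2)·mean² / ((1+3ρ)/4) = 16·mean²/0.7, df 1 and 62.
- Interaction: λ = (n/2)·Σ(diff−mean)² / (1−ρ) = 16·Σ/0.4, df 3 and 186.
- Baseline-adjusted week 12: λ = (n/2)·D² / (1−ρ²) = 16·D²/0.64, df 1 and 61.

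| Profile | Main effect | Interaction | Baseline-adjusted week 12 |
|---|---|---|---|
| 0, 0.6, 0.6, 0.6 | λ = 16 × 0.2025/0.7 = 4.63, 56% | λ = 16 × 0.27/0.4 = 10.8, 79% | λ = 16 × 0.36/0.64 = 9.0, 84% |
| 0, 0.2, 0.4, 0.6 | λ = 16 × 0.09/0.7 = 2.06, 29% | λ = 16 × 0.20/0.4 = 8.0, 64% | λ = 9.0, 84% |

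As a check on meaning, a 0.6 SD gap at all four visits, baseline included, gives main-effect power 0.81 and interaction power 0.05. The main effect does not measure change.

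**5. The scale of 0.3.** The boundaries 0.2/0.5/0.8 are those for d, on which 0.3 is small. But 64 arises only with f = 0.3, that is d = 0.6. With d = 0.3 (f = 0.15), the same main-effect test needs 248.

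**6. What 64 evaluable patients support at week 12, baseline-adjusted.** Solving for 80% power gives D = 0.57 SD at correlation 0.6 and 0.65 SD at correlation 0.4. For D = 0.3 and correlation 0.6, λ = 16 × 0.09/0.64 = 2.25 and power is about 31%; 80% would need 226 evaluable.

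**The case against.** - **The option is not stated.** The article never says which G*Power routine was used. This stands: the group main effect is an inference. It is a strong one, because it returns 64 exactly and no interaction or 12-week variant tried does.
- **The main effect may be a test the trial uses.** The group*time notation can be read as listing the two factors, and the group F is part of the same ANOVA output. The sentence on 12-week change is not a formally defined primary contrast. This also stands in part. A reader might infer that the trial was powered for a test it will not use; the documents do not go that far. They support only that the article emphasises other comparisons and nowhere singles out a visit-averaged group effect.
- **No clear direction of harm.** If 0.3 is taken as f for the interaction, 64 patients give power above 0.99 (default option) or about 0.94 (other conventions). If it is d = 0.3 at week 12, power is about 31% even with baseline adjustment. So neither too small nor too large follows from the mismatch alone.
- **It is not an arithmetic error.** Correct: 64 and 86 both follow from the inputs. The fault is that the powered effect and the emphasised analysis do not match.

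None of this supplies a stated power for group-by-time or for week 12. Nor is it detail left to a fuller document, since the article gives a power claim that does not fit its own analysis and outcome sections.

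**Conclusion.** The point holds as a mismatch between the powered effect and the emphasised comparison. The stated 80% power reproduces only for a between-group effect averaged over four visits including baseline, and cannot be read as the power for group-by-time or for the 12-week change. Reaching it requires about 0.8 SD at every post-baseline visit. For the two profiles examined, the main effect is the least sensitive of the three tests at a week-12 difference of 0.6 SD.

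The reproduction of 64 needs only the protocol's own inputs. The comparative powers also rest on compound symmetry, correlation 0.6, 32 evaluable per arm and the assumed profiles. The f-versus-d conflict is separate but compounds the problem: the article describes a small effect while its number corresponds to d = 0.6.

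A reader might go on to infer that 86 is wrong, or that 86 is safe. The documents support neither until the sponsor says which contrast and which effect size were intended.

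**What to change.** 1. Name one primary contrast, in the same words, in Sample size calculation {14} and in Statistical methods {20a}. An example is the between-group VAS difference at week 12, adjusted for baseline or estimated from a mixed model. Changing only the sample-size paragraph would create a new mismatch, because {20a} does not now plan a baseline-adjusted week-12 contrast.
2. Restate power on the scale of that contrast. For the example, 64 evaluable patients at two-sided 5% give 80% power for about 0.57 SD (correlation 0.6) to 0.65 SD (correlation 0.4).
3. Say whether 0.3 was meant as f or d. If d = 0.3 was intended, state that power for this contrast is about 31% at correlation 0.6.
4. Remove the 80% claim tied to the four-measurement ANOVA, and state openly that the planned 86 detects a medium rather than a small effect. The 0.57 to 0.65 SD range describes what 64 can detect; it does not justify the size, so the sponsor must say whether that range is acceptable.

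The cost is edits to two sections and a less favourable stated detectable effect. If the sponsor does not accept that effect, the sample size itself has to be reconsidered.
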